### Trial structure

At time T0, for patients randomized in the study, the following information is collected:Demographic variables: age and genderClinical variables: ejection fraction, NYHA class, and comorbiditiesThe Cumulative Illness Rating Scale (CIRS) [29] measures the patient’s health status. Each item is evaluated according to an ordinal scale with increasing levels of severity: from 1 (absent pathology) to 5 (very severe pathology). Two measures are obtained:Severity Index (SI): the average of the scores of the first 13 categories (the maximum obtainable score is 5)Comorbidity Index (CI): the category numbers with equal or higher scores.

At times T0 and T6, in all patients randomized, the following information is collected:Physical variables: body mass index (BMI), abdominal circumferenceBiochemical parameters: glycated hemoglobin (HbA1c) and the amino-terminal fragment of Brain Natriuretic Peptide (NT pro-BNP).Evaluation of exercise capacity by the 6-min walk test (6MWT) [30, 31].The Physical Activity Scale for the Elderly (PASE) [32] assesses physical activity performed during the previous period.Quality of life is measured in the following ways:The Minnesota Living Heart Failure Questionnaire (MLHFQ) [33]. MLHFQ comprises 21 topics that evaluate how, over the past month, the various physical and emotional symptoms of HF have prevented you from living as you would like.The Diabetes Quality of Life (DQOL) questionnaire [34]. DQOL comprises 46 questions that investigate four areas: general satisfaction, the global impact of the disease, concerns about social relationships, and concerns about diabetic disease. The scores on each scale range from 0 to 100; higher scores correspond to a better quality of life.The validated Italian version of the 12-item Short Form Survey (SF-12) questionnaire [35, 36]. The SF12 has a 6-item Physical Component Summary (PCS) and a 6-item Mental Component Summary (MCS).

Only in the patients of the IG are evaluated the weekly mean in the number of steps from baseline over the 6 months of follow-up, and at T6:Satisfaction with care. Six items, with a score from 0 (not at all satisfied) to 4 (very satisfied), investigate the service as a whole, the use of the devices, the willingness of healthcare professionals to respond to the patient’s needs, the clarity of indications to the suggestions provided, the feeling of support, and whether the service is perceived as a real help or not (Table 1).Usability of the devices and the app through the System Usability Scale (SUS) [37–39].

**Table 1 Tab1:** Customer satisfaction

1. **How do you judge the system overall?**	
a. Not satisfying at all	0
b. Poorly satisfying	1
c. Fairly satisfying	2
d. Quite satisfying	3
e. Very satisfying	4
2.Was it easy to use devices?	
a. Very complicated	0
b. Quite complicated	1
c. Complicated	2
d. Quite easy	3
e. Very easy	4
3. **Did you experience difficulties in contacting the service?**	
a. Very frequently	0
b. Frequently	1
c. Sometimes	2
d. Rarely	3
e. Never	4
4. **Were the indications of the health staff clear?**	
a. Not at all	0
b. Poorly clear	1
c. Fairly clear	2
d. Quite clear	3
e. Very clear	4
5. **Do you feel more secure since when you have access to the service?**	
a. Not at all	0
b. Poorly	1
c. Fairly	2
d. Much	3
e. Very much	4
6. **Did the access to the service help your family or the people you live with?**	
a. Not at all	0
b. Poorly	1
c. Fairly	2
d. Much	3
e. Very much	4

The complete treatment and assessment phases are available in Fig. 2.

**Fig. 2 Fig2:**
[figure not shown]
Complete treatment and assessment phases

### Technology support

The protocol makes use of two main components:
✓ HealthPlatform web portal and app (CompuGroup Medical SE, CGM, Italy)✓ TreC Cardio web portal and app (Fondazione Bruno Kessler, Trento, Italy)

And two wearable devices:✓ Electrocardiograph (Hi – ECG 3 leads device, CompuGroup Medical SE, CGM, Italy)✓ Tracker bracelet Fitbit Inspire 2 (https://www.fitbit.com/)

HealthPlatform is a software platform consisting of a web portal for patient management by healthcare personnel and an Android/iOS smartphone app used by patients for clinical data collection and communication with doctors and nurses. The HealthPlatform system is Medical Device Class IIa certified, and the channel between the app and the back-end is protected using the Transport Layer Security protocol (TLS with encryption).

The platform acquires:Vital parameters through a Hi-ECG device with three leads transmit electrocardiogram traces to a smartphone via Bluetooth. The collected data are saved on the smartphone’s internal app database and associated with the user. The smartphone app is a gateway to recognize the associated ECG and sends the data to the server via the HealthPlatform web platform.The fitness data recorded by the tracker automatically flows to the Fitbit App and the Fitbit server and will be retrieved daily from the HealthPlatform server. Data acquisition via Bluetooth is carried out directly by the Fitbit app, which sends them to the Fitbit server independently from the HealthPlatform app. The HealthPlatform server’s task is to interface directly with the Fitbit server and retrieve the data associated with the user daily (the integration is, therefore, server-to-server side).

The doctor/health personnel can access a specific section of the HealthPlatform web portal using personal credentials to view patients’ electrocardiographic traces and FitBit data.

The “TreC Cardio” platform includes a web dashboard for healthcare personnel to manage patients and an Android/iOS app for patients to collect clinical data and communicate with doctors and nurses. With the “TreC Cardio” app, patients can:View their medication history and upcoming dosesConfirm whether they have taken their daily therapy or provide a justification for not taking itEnter, view, and modify self-detected clinical parameters and symptomsReceive reminders for healthcare actions (e.g., measuring blood pressure)Chat, send images/PDFs, and make video calls with healthcare personnel

Once authenticated, healthcare personnel in the web dashboard can:Enroll new patients and activate the TreC Cardio app for themManage individual patient treatment plans by activating therapies prescribed by specialists and tasks/actionsRemotely monitor patient data and view entered data trendsDeliver questionnaires via chatbotChat and conduct video calls with patients

Figure 3 represents the technology model of the protocol.

**Fig. 3 Fig3:**
[figure not shown]
Technology model of the protocol

### Interventions

#### Intervention group

Patients in the IG group are followed through a remote home telemedicine program for 6 months, in addition to standard care, such as visits to the general practitioner and hospital control on request.

The telemedicine program is characterized by the following:Supporting from a nursing case manager through a structured teleassistance program (phone or video calls at least once a week)Cardiology and diabetes teleconsultation at the beginning and in case needed during the program.Support of the trainer to stimulate daily physical activityTelemonitoring of patient vital signs (e.g., single electrocardiographic trace) and daily steps via a trackerAn app for recording and monitoring parameters: daily drug treatment and clinical parameters

#### Intervention program

Upon enrollment, the patients receive the tracker bracelet, the electrocardiograph device, and a smartphone with pre-installed apps for receiving the respective information on wearable devices.

The Nurse Case Manager coordinates activity and promotes patient learning of disease self-management techniques to prevent exacerbations; she/he plays a central role in all home care continuity interventions, becoming a key interface in the dialogue between patients and specialists.

The educational plan involves family members and is crucial to the program’s success.

An agenda of scheduled contacts is shared with the patient.

During the teleassistance program in the 6-month home-based study period, the nurse:Collects information regarding medical history and symptomsProvides health education and trainingVerifies prescription adherenceEvaluates general well-beingAssesses the level of assistance provided by the caregiverUpdates the computerized clinical fileActivates specialist intervention for a teleconsultation if necessary

Patients can contact their nurse during operating hours for clinical, symptom, or treatment-related issues.

Patients are encouraged to perform physical activity at least thrice a week, reinforcing the importance of lifestyle changes and exercise, asking them always to wear their Fitbit to monitor their daily steps constantly.

Furthermore, the patients are encouraged to update the “TreC Cardio” app information by entering any symptoms and biological parameters (blood pressure, heart rate, weight, blood sugar, etc.), viewable by the nurse on the web dashboard.

The healthcare personnel will be able to remotely manage the treatment path of the individual patients enrolled by prescribing therapies and tasks, view the progress of the clinical parameters collected and entered by the patient (e.g., vital signs, symptoms), interact with the patient through a chat for exchange of text messages and the sending of multimedia files by the patient, activate a videoconference, and deliver questionnaires.

The research team continuously monitors the data to ensure patients comply with the intervention. Patients are contacted if the nurse receives signs and symptoms of a worsening clinical condition to resolve problems with device malfunctions or in the event of failure to enter information into the app.

### Control group

After the baseline assessments required by the program, patients in the CG receive standard care, including visits from their general practitioner and in-hospital controls upon request. Patients are informed about the importance of maintaining a healthy lifestyle and encouraged to engage in daily physical activity. Information leaflets on disease management and physical activity are provided. Final evaluations will occur at the 6-month cardiological visit.

#### Outcome assessments

##### Primary outcome measures

The primary outcome is exercise tolerance improvement measured by the difference in the meters walked at the 6MWT. The test measures the distance walked when subjects are asked to walk as fast as possible for 6 min, and performance in this test has been used to measure cardiovascular exercise capacity, particularly in patients with congestive heart failure [30] and diabetic patients [31].

##### Secondary outcomes measures

The improvement of the physical activity profile by the PASE, a self-reported questionnaire of occupational, household, and leisure items over 1 weekImprovement of QoLImprovement of the disease status (NT pro-BNP, HbA1c)Reduction of hospitalizations for all causes

#### Withdrawal

According to Italian research ethics legislation, we inform the patients about their rights as subjects in a scientific trial and their discontinuation rights. We do this to make patients consider participation thoroughly to diminish the likelihood of dropping out. Patients can withdraw from the trial at their request or the request of their legal representative at any time. Every withdrawal is recorded in the “personal health record” of the patient.

#### Data collection, management, and analysis

We use RedCap, an eCRF web tool, to manage anonymized surveys and databases. Each hospital stores personally identifiable information and clinical variables; only authorized personnel can access the data. The project manager and nurse hold the code list connecting personal identifying data to the individual participant. The principal investigator from each hospital is responsible for securing and monitoring data collection and interpretation, as well as being involved in project management, analysis of samples, data collection, and observations, and they will jointly interpret the results.

All adverse events that occurred during the 6-month study observation period will be reported in the final paper. All serious and unexpected adverse events will be reported to the Ethics Committee as required.

#### Sample size

Based on the literature analyzed [40, 41] of the experience developed over the years in patients with heart failure [42] and patients with a complex phenotype, SCC and COPD [19], followed by remote surveillance, we estimated a sample of 240 patients who could be evaluated to demonstrate efficacy on the primary outcome. The number should be sufficient to establish an anticipated difference of 45–50 m in walking distance at the 6MWT (primary endpoint) between the intervention and control group to demonstrate a statistically significant difference between groups applying a *t*-test with alpha = 0.80 and beta = 0.05. A mean of 360 m (SD = 115) was considered. We performed a comparison test between two independent means (unpaired data) with equal sd (sd1 = sd2 = sd) in the two groups. Therefore, assuming an SD = 115 and delta = 28,217, the sample is 208 patients, 104 per group. Thus, considering the 15% of patients not present at T6 for calculating the endpoint (dropout), the sample becomes 239.

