### Randomization

Patients are screened in the outpatient departments of the three hospitals during routine HF visits. A Nurse Case Manager reviews the scheduled office visits and personal electronic records weekly to identify patients eligible for the study. The study physician verifies their eligibility based on the inclusion criteria during the office visit and screens any other patients. All eligible patients are asked to participate, and those who give their consent are randomized (1:1) into either the intervention (IG) or control group (CG). Patients are allocated using a computer-generated table in fixed blocks of four, with the allocation sequence concealed from investigators to prevent selection bias. A separate randomization list is created for the three centers involved.

Due to the intervention’s nature, the patients and physicians know group allocation. However, outcome assessors and data analysts will be blinded to the allocation.

We have standardized the nursing approach as much as possible by conducting joint staff training, organizational meetings, and planning before patient enrolment in the three hospitals involved.

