### Statistical analysis

Statistical analysis will be carried out by a certified health professional using STATA software (College Station, TX, USA). Data will be descriptively analyzed and presented as percentage or mean ± standard deviation for all clinical variables, median ± interquartile (IQ) range for variables without a normal distribution, and percentage for categorical and binary variables. The Kolmogorov–Smirnov test will test the distribution and normality of variables. To compare groups at T0, the Student *t*-test, the Mann–Whitney-Wilcoxon test for continuous variables, and the chi-squared test for categorical variables will be used.

Two-way analysis of variance (ANOVA) will analyze the effects of the intervention for repeated measures (time and group). A post hoc analysis will be conducted when the ANOVA *F* ratio is significant for the Student *t*-test among times and groups, and Bonferroni’s correction will be applied. Statistical significance is defined as *P* = 0.05.

Data will be primarily analyzed according to the intention-to-treat principle. An on-treatment analysis will be subsequently performed to assess whether protocol deviations have caused bias. Participants with documented deviation from the study protocol (i.e., patients in the intervention group who received only some of the intervention or participants in both groups with incomplete follow-up data) will be excluded.

No interim analysis is planned as no harm to patients is expected from this trial. There is no reason to stop prematurely other than the end of the financing.

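### The sample-size section states alpha = 0.80 and beta = 0.05, which are unusable as design values and do not give the planned 208 patients; two-sided alpha 0.05 with 80% power does.

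*Protocol article*

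**What the plan says.** The Sample size section of the protocol article describes a t-test "with alpha = 0.80 and beta = 0.05", intended to detect "an anticipated difference of 45–50 m in walking distance at the 6MWT (primary endpoint) between the intervention and control group". On variability it says: "A mean of 360 m (SD = 115) was considered". The method is a "comparison test between two independent means (unpaired data) with equal sd (sd1 = sd2 = sd) in the two groups", and the result is given as "assuming an SD = 115 and delta = 28,217, the sample is 208 patients, 104 per group". Allowance for 15% dropout then takes the total to 239.

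The Statistical analysis section gives a different significance level: "Statistical significance is defined as *P* = 0.05". It does not say whether the test is one- or two-sided. Nowhere does the article state a power of 0.80 or a beta of 0.20.

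**The concern.** Alpha is the probability of a false-positive result and beta is one minus power. As printed, the trial would accept an 80% chance of declaring a difference when there is none, and would have 95% power. The first value is unusable and conflicts with the 0.05 in the Statistical analysis section. The second is a level of power that the stated sample may not deliver.

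The obvious guess, that the two labels changed places, does not repair the sentence: alpha = 0.05 with beta = 0.80 is a trial with 20% power. One of the numbers must be a power that has been labelled as an error rate.

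What is at stake is how the primary result is read, above all a null result. With beta = 0.05, a non-significant comparison would count as strong evidence against a 45 m benefit; with beta = 0.20 it is considerably weaker evidence. An ethics committee, funder or later reader also cannot reproduce the calculation from the values given.

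**Working it through.** **Inputs from the Sample size section:** difference 45 m (lower end of the stated 45–50 m), SD 115 m in both groups, unpaired comparison of two means. Allocation is 1:1 (Randomization section). **Assumption:** a two-sided test, since the article does not state sidedness.

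**Formula (normal approximation), patients per group:**

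n = 2 × (SD/difference)² × (z for 1 − alpha/2 + z for power)²

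with 2 × (115/45)² = 13.06. The exact figures come from the noncentral t distribution, because the protocol names a t-test.

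**1. Reproducing the protocol's figure.** Two-sided alpha 0.05, power 0.80: 13.06 × (1.960 + 0.842)² = 102.5, so 103 per group. The exact t-test gives 103.5, so 104 per group and 208 in total. This is the protocol's number.

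**2. Alternative readings at 45 m, two-sided:**

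| Reading | alpha | power | n per group, normal | n per group, exact t |
|---|---|---|---|---|
| As printed | 0.80 | 0.95 | 48 | 38 |
| Labels exchanged (beta = 0.80) | 0.05 | 0.20 | 17 | 18 |
| 0.05 from the analysis section, printed beta | 0.05 | 0.95 | 170 | 171 |
| Conventional values | 0.05 | 0.80 | 103 | **104** |

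The two methods differ for the printed pair because, at alpha = 0.80, rejections in the wrong direction are common. The normal formula ignores them and the exact calculation counts them. A one-sided 0.05 test with 80% power needs 81 (normal) or 82 (exact) per group, so it does not give 104 either.

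**3. Cross-check on the inputs.** The paragraph also prints a delta of 28,217. The noncentrality parameter of the t-test for 45 m and 104 per group is

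45 / (115 × √(2/104)) = 45 / 15.948 = 2.8217

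The digits are identical and only the decimal mark differs. This indicates that the run behind the text used 45 m and 104 per group, and that the printed delta is not a distance in metres. Read as 28.217 m, it would leave 104 per group with about 42% power at alpha 0.05.

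**4. Power with 104 evaluable patients per group, two-sided alpha 0.05 (exact t):** 80.2% at 45 m and 87.7% at 50 m. Neither end of the anticipated range reaches 95%. That power would need 171 per group (342 in total) at 45 m, or 139 per group (278 in total) at 50 m.

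**The case against.** The strongest reply is that nothing in the design is wrong. The figure of 208 is exactly right for two-sided alpha 0.05, 80% power, 45 m and SD 115 m, and the digits of the misprinted delta show that the calculation was run that way. The analysis will apply 0.05, so no result will be declared significant at 0.80. The article never uses the words 95% power. That figure arises only if the printed beta is kept while its partner alpha is discarded, and an informed reader will recognise 0.05 and 0.80 as the usual significance level and power under the wrong labels. On this view it is a labelling slip.

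Much of this stands. The number of patients and the test are unaffected, and the comparison with 342 patients must not be read as a shortfall in recruitment. The values are also mathematically admissible; they are simply not usable for design. Furthermore, the 80% holds for 208 evaluable patients. If 240 are randomised and 15% are lost, 204 remain (102 per group) and power at 45 m is 79.4%.

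It does not remove the point. The error rates are core parameters of the primary sample-size statement. Both are printed wrongly, one of them contradicts another section, and no other sentence supplies the correct values. A power of 95% is what a beta of 0.05 means, and a reader who takes alpha from the analysis section will arrive at it.

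**Conclusion.** The concern holds. The printed alpha and beta cannot be the values behind the 208 patients, and the printed alpha contradicts the 0.05 level set for the analysis. Of the readings tried, only two-sided alpha 0.05 with power 0.80 reproduces 104 per group. Taken with the 0.05 level, the stated beta of 0.05 overstates power by about 15 percentage points at 45 m (95% against 80.2%) and by about 7 points at 50 m (95% against 87.7%). It understates the type II error at 45 m by a factor of four (0.05 against 0.20).

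This rests on the protocol's own difference, SD and test, on two-sided testing, and on 104 evaluable patients per group. It is an error of reporting in a statement on which the trial relies. It is not evidence that the trial was sized wrongly.

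**What to change.** Replace the error rates in the Sample size section with wording such as: two-sided t-test, alpha = 0.05, power = 0.80 (beta = 0.20), difference 45 m, SD 115 m, giving 104 evaluable patients per group (208 in total). State in the Statistical analysis section that the 0.05 level is two-sided, so that both sections carry the same single level.

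In the same edit, correct the printed delta. Either give it as the noncentrality parameter, 2.8217, if that is confirmed as the intended quantity, or delete it. Otherwise the paragraph will still appear to contain a second effect size.

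The cost is a text correction, carried into any other trial document that repeats the sentence. For this point the number of patients, the test and trial conduct do not change.

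### The 15% dropout allowance is applied as 208 × 1.15 instead of 208/0.85, so 239–240 enrolled leave about 203–204 with a T6 endpoint, 4–5 short of the stated 208 (minor)

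*Protocol article*

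**What the plan says.** All the figures are in the Sample size section of the protocol article. It opens with the total: "we estimated a sample of 240 patients who could be evaluated to demonstrate efficacy on the primary outcome". It anticipates a difference of 45–50 m in the 6-min walk test and describes the method as a "comparison test between two independent means (unpaired data) with equal sd" in the two groups, with an SD of 115 m. The result is that "the sample is 208 patients, 104 per group". The last step allows for attrition: "considering the 15% of patients not present at T6 for calculating the endpoint (dropout), the sample becomes 239".

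Read in sequence, 208 is the number needed with a T6 measurement, and 239, given as 240 at the start, is the number to enrol.

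**The concern.** A dropout allowance should leave the calculated number once the assumed loss has occurred. The section defines the 15% as the share of patients who will not be present at T6 for the endpoint. That is a share of those enrolled, so the required number has to be divided by 0.85. Adding 15% of 208 to 208 is a different calculation and always gives too small a total.

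At stake is whether the trial reaches its own target under its own assumption. The 208 gives almost exactly 80% power at the lower end of the anticipated range, so there is little reserve to absorb a shortfall. The Limitation section also tells the reader that attrition was taken into account when the sample size was calculated.

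**Working it through.** **Inputs.** From the Sample size section: SD 115 m, difference 45–50 m, 208 patients (104 per group), 15% loss, totals 239 and 240. From the Randomization section: 1:1 allocation.

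Two readings are needed:
- The section prints "alpha = 0.80 and beta = 0.05". I take the labels as swapped, meaning alpha 0.05 and power 0.80, in line with the 0.05 level in the Statistical analysis section. Sidedness is not stated. I assume two-sided, because that reproduces 104 per group at 45 m, whereas one-sided gives about 82.
- The section also prints "assuming an SD = 115 and delta = 28,217". Read as 28.217 m, this does not lead to 208: it would need about 262 per group. The 208 follows from 45 m, which is used below. These misprints are separate matters and do not affect the dropout step.

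**Step 1: reproduce 208.** Normal approximation, per group: n = 2 × SD² × (z₀.₉₇₅ + z₀.₈₀)² / δ² = 2 × 115² × (1.960 + 0.842)² / 45² ≈ 102.5, so 103. The exact two-sample t-test gives 103.5, so 104 per group and 208 in total, as stated.

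**Step 2: reproduce 239.** 208 × (1 + 0.15) = 239.2. This is the printed figure, and 240 when rounded up.

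**Step 3: the step that keeps 208.** 208 / (1 − 0.15) = 244.7, so 245, or 246 (123 per arm) for equal arms. Check: 245 × 0.85 = 208.25.

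**Step 4: what the printed totals leave after 15% loss.**
- 239 × 0.85 = 203.15, about 5 short of 208.
- 240 × 0.85 = 204.0, which is 4 short of 208.

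**Step 5: the loss that the printed totals can absorb.**
- 1 − 208/239 = 13.0%
- 1 − 208/240 = 13.3%

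**Step 6: power (unpaired t-test, SD 115 m, two-sided 0.05).**

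| Patients with T6 endpoint | Power at 45 m | Power at 50 m |
|---|---|---|
| 208 | 80.2% | 87.7% |
| 204 | 79.4% | 87.1% |
| 203 | 79.2% | 86.9% |

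The difference detectable with 80% power moves from 44.9 m with 208 to 45.3–45.4 m with 203–204.

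**The case against.** The strongest reply is that nothing of consequence follows. The shortfall in enrolment is 6 patients (245 against 239, or 246 against 240), about 2.5%. Power at 45 m falls by 1 point or less, and 80% power still holds over nearly all of the 45–50 m range. The 15% is itself a round planning guess, and a loss of about 13% would leave the target intact. All of this stands, and it is why the point is minor. It does not make the printed step correct: the plan states a 15% loss and a need of 208, and its enrolment figure does not reconcile the two.

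The power figures also describe the t-test used for planning. The Statistical analysis section specifies a repeated-measures ANOVA by time and group. With two time points, its group-by-time test amounts to a t-test on change, whose SD under equal variances is 115 × √(2(1 − ρ)). That is below 115 if the correlation ρ between baseline and T6 exceeds 0.5, and above 115 if ρ is lower. The protocol gives no ρ, so power under that analysis could differ from the planning figure by more than the dropout error does. This objection also stands, so the restated power should be tied explicitly to the unpaired t-test.

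In the other direction, a reader might infer from the opening sentence that the plan promises 240 patients with T6 data. On that reading it would overstate its evaluable number by 240 − 204 = 36 and claim about 86% power. The document does not support this. The opening wording is loose and defines no analysis population. The same paragraph shows that the total already contains the dropout allowance, and no stated power rests on 240 completers. The wording should be cleaned up, but it is not a 36-patient error.

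**Conclusion.** The concern holds as a minor arithmetic error. The plan multiplies by 1.15 where its own definition of dropout calls for division by 0.85. With 239–240 enrolled and 15% lost, about 203–204 patients have the endpoint, 4–5 fewer than the stated 208. Power at 45 m is about 79% instead of 80%, and at 50 m about 87%.

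The counts follow directly from the printed figures. The power values rest on two-sided alpha 0.05, SD 115 m, a 45 m difference as the basis of the 208, and an unpaired t-test.

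A reader might also infer that adjusting for the baseline walk distance would win back the loss. That may be so, but it depends on a correlation that the protocol does not report, so it should not be offered as reassurance.

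**What to change.** Keep enrolment at 240 and correct the text of the Sample size section:
- State that 240 is the number to be randomized, and replace the clause in the opening sentence that describes these patients as evaluable.
- Replace the final step with wording such as: *240 patients will be randomized; with 15% missing at T6, about 204 (102 per arm) are expected to be evaluable, giving about 79% power to detect a 45 m difference with a two-sided unpaired t-test at the 5% level and an SD of 115 m.*

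The cost is wording, plus a stated power about one point less favourable. No change to design, recruitment or analysis is needed.
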